## Abstract

**Background:**

Colorectal cancer (CRC) is the most common cancer affecting both men and women in Australia. The illness and related treatments can cause distressing adverse effects, impact on emotional and psychological well-being, and adversely affect social, occupational and relationship functioning for many years after the end of treatment or, in fact, lifelong. Current models of follow-up fail to address the complex needs arising after treatment completion. Strategies to better prepare and support survivors are urgently required. We previously developed a nurse-led supportive care program (SurvivorCare) and tested it in a pilot study involving 10 CRC survivors. The intervention was found to be highly acceptable, appropriate, relevant and useful.

**Methods/design:**

This study is a multisite, randomised controlled trial, designed to assess the impact of the addition of the SurvivorCare intervention to usual post-treatment care, for people with potentially cured CRC. SurvivorCare comprises the provision of survivorship educational materials, a tailored survivorship care plan, an individually tailored nurse-led, face-to-face end of treatment consultation and three subsequent telephone calls. Eligible patients have completed treatment for potentially cured CRC. Other eligibility criteria include stage I to III disease, age greater than 18 years and adequate understanding of English. All consenting patients complete questionnaires at three time points over a six-month period (baseline, two and six months). Measures assess psychological distress, unmet needs and quality of life*.*

**Discussion:**

This supportive care package has the potential to significantly reduce individual suffering, whilst reducing the burden of follow-up on acute cancer services through enhanced engagement with and utilisation of general practitioners and community based services. If the intervention is successful in achieving the expected health benefits, it could be disseminated readily. All training and supporting materials have been developed and standardised. Furthermore, the intervention could easily be adapted to other cancer or chronic disease settings.

**Trial registration:**

Australian New Zealand Clinical Trial Registry ACTRN12610000207011.

## Background

In Australia, bowel cancer is the most common cancer affecting both men and women [1]. Although it is the second highest cause of death from cancer (after lung cancer), many people are long-term survivors. Survivors of bowel cancer represent the third largest group of long-term cancer survivors in the Western world (after survivors of breast and prostate cancer) with five-year survival rates of approximately 55% [2]. It is expected that the number of people affected by and surviving bowel cancer will rise significantly over the next 10 years. Australian data showed a 30% increase in the number of new or surviving cases of colorectal cancer (CRC) in women and 33% for men between 2001 and 2011 [1].

CRC survivors are vulnerable to a number of distressing long-term sequelae [3-8]. Forty percent of people thought to be cured will ultimately develop recurrent disease [9]. In addition, survivors of CRC are at increased risk of developing a second cancer, either bowel cancer or another primary cancer [9]. Survivors are susceptible to surgical complications, such as bowel obstruction, abdominal wall hernias and altered bowel function [4,5].

Rectal cancer survivors are at risk of faecal, bladder and sexual dysfunction [5-8]. Bowel dysfunction may include faecal frequency and urgency, faecal leakage, and the need to use pads. Surgery and radiation treatment for rectal cancer may result in long-term and late consequences, such as chronic diarrhoea, poor food absorption, potential early menopause in some women, loss of fertility in both men and women, damage to the vagina and impaired ability to achieve erections [6-9]. Chemotherapy can result in persistent peripheral neuropathy resulting in pain and loss of function, impacting upon activities of daily life.

Given these serious side-effects, not surprisingly social, occupational and relationship functioning commonly suffer [9-13]. Many survivors do not return to full-time work, or may have a delayed return to work [14]. This, in addition to out of pocket expenses, can impose a significant financial burden [10,11]. Some survivors experience reduced social integration and changes in their intimate relationships. Many suffer ongoing psychosocial distress, especially those managing permanent colostomies [7,8,10]. Studies suggest an increased rate of depression compared with matched groups unaffected by cancer [12]. Schag and colleagues found, even at five-year follow-up, that many colon cancer survivors reported difficulties with physical functioning, poor energy levels, difficulty undertaking recreational activities, ongoing concerns about recurrence, body image concerns, problems with sexual interest and functioning, and work problems [13]. Despite these significant challenges, colorectal cancer survivors are underrepresented in survivorship research in general [15]. The current investigators were unable to identify any published research describing interventions to better support bowel cancer survivors following treatment completion.

The current project seeks to evaluate an innovative nurse-led supportive care program (SurvivorCare). The intervention was developed by experts and key stakeholders in supportive care research after extensive quantitative and qualitative research with colorectal cancer survivors (consumers) and health care professionals [16,17]. Consumer and health care professionals’ perspectives were sought to determine the relevance of the proposed Survivorship Care Plan (SCP) elements [16]. Specifically, the intervention is designed to: 1) be patient-centred by eliciting individual concerns and needs to direct personal health care plans; 2) provide comprehensive post-treatment care coordination by a specialist intervention nurse to address the multifaceted supportive care post-treatment needs of this patient group; 3) provide instruction in evidence-based self-care and stress reduction strategies to better enable people to manage self-care requirements in the period of cancer survivorship following treatment completion; 4) provide tailored information to patients and their significant others in order to maximise information relevance to this specific survivorship period; 5) if not already implemented, coordinate appropriate post-treatment care referrals to community and multidisciplinary health professionals where relevant; and 6) provide a sustainable model of nurse-led survivorship care centred on standardised end of treatment processes and enhanced collaboration and communication with primary care.

The complete SurvivorCare package (DVD, booklet, Question Prompt List (QPL), Survivorship Care Plan (SCP), end of treatment session and telephone follow-up) was trialed with 10 participants to examine appropriateness, acceptability and clinical feasibility in a pilot test trial. SurvivorCare proved to be a well-received, comprehensive intervention by the participants and nurses [18].

### Study aim

This study seeks to examine the effectiveness of an innovative supportive care program (SurvivorCare) comprising survivorship educational materials, provision of a tailored SCP, an individually tailored nurse-led end of treatment consultation and telephone follow-up for people with potentially cured colorectal cancer, aiming to reduce psychological distress and unmet needs in the six months following treatment completion.

### Study hypotheses

#### Primary endpoint

CRC survivors allocated to the SurvivorCare intervention will report a significant relative benefit for psychological distress compared to survivors in the control group from baseline to Follow-up 1 (eight weeks after randomisation for the usual care group, and eight weeks after the first intervention session for the SurvivorCare group).

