### Recruitment process

Patient eligibility is confirmed with the treating clinician. The study is further explained to patients by a trained data manager and written consent is obtained. Patients are approached zero to six months prior to the end of treatment (preferably), or up to six months after the end of treatment. Once the study coordinating centre receives a patient randomisation request by fax or email from a participating site, the patient is randomised 1:1 to either usual care or SurvivorCare (100 patients are expected in each arm). The type of treatment and hospital site is entered in an Access database, where the allocation is balanced by site using a minimisation method. Figure 1 illustrates a schematic diagram of the study design.

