### Intervention group/SurvivorCare

The intervention consists of four main components: (1) information package; (2) nurse-led face-to-face end of treatment session; (3) SCP; and (4) telephone follow-up.

(1) Information package

The package includes a DVD (Just Take It Day to Day) [19], a booklet (*Life After Cancer*) [20], and a Question Prompt List (QPL). The QPL is a list of 70 questions covering common issues cancer survivors encounter in the first year following treatment. Ten main topics covering issues and concerns around coping, physical consequences of completing treatment, late and long-term effects of treatment, impact on family and friends, recurrence, follow-up planning, fertility, pregnancy and menopause, sexuality, dealing with practical matters, such as finances, returning to work and insurance, and need for further information and support, are listed to help the patient think about what they might like to ask their nurse or doctor. The patient is asked to view the material and complete the QPL prior to the nurse-led face-to-face session.

(2) Nurse-led face-to-face session

A nurse-led end of treatment session will take place in a standard timeframe after randomisation. Focus group results and a review of the literature [17] and expert input were used to design the end of treatment session, which addresses current concerns, seeks to attain a sense of closure on treatment and aims to prepare people for the survivorship phase and introduce telephone follow-up. The session takes place in a private hospital clinic room by a nurse trained to deliver the intervention. Session time is 60 to 90 minutes. Significant others are encouraged to also attend the end of treatment consultation to maximise the positive impact on patient outcomes [21,22]. Additional concerns not covered in the session are covered in subsequent telephone follow-up sessions. The session incorporates seven elements.

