### Data collection procedure

Participants will be asked to complete a baseline questionnaire on the day of randomisation and two subsequent follow-up questionnaires at eight weeks (Follow-up 1) and six months (Follow-up 2) after the face-to-face session for the intervention group or after randomisation for the usual care group. Table 2 shows data to be collected.

**Table 2 T2:** Time points measuring patient reported outcomes for the SurvivorCare study

**Time point**	**Questionnaire**
Baseline: on the day of randomisation (zero to two weeks before a potential first intervention session)	Demographic variables, Medical records, BSI-18, DT, CaSUN, EORTC QLQ C-30 and CR-29.
Follow-up 1: eight weeks after randomisation date for usual care patient or after the first session date for intervention patients	BSI-18, DT, CaSUN, EORTC QLQ C-30 and CR-29 and Satisfaction Measure with usual care checklist
Follow-up 2: six months after randomisation date for usual care patient or the first session date for intervention patients	BSI-18, DT, CaSUN, EORTC QLQ C30 and CR-29

BSI-18, Brief Symptom Inventory; CaSUN, Cancer Survivors’ Unmet Needs Measure; DT, Distress Thermometer; EORTC QLQ C-30, European Organisation for Research and Treatment of Cancer core questionnaire; EORTC QLQ CR-29, the colorectal cancer module.

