### Statistical analysis

Analyses will be by intention-to-treat and performed in SPSS Windows Version 21.0 (or higher) (Chicago, IL, USA). Prior to formal analyses, descriptive statistics and graphical displays will be used to identify missing and out-of-range values, assess the distributional characteristics of test scores and summarise study measure completion rates and missing data points. Responses to the BSI-18, DT, CaSUN, EORTC QLQ C-30 and CR-29 will be scored according to algorithms in the users’ manuals for these instruments.

Descriptive statistics will be used to summarise baseline demographic and clinical characteristics of patients randomised to the intervention and usual care. Recruitment bias and possible differential attrition will be assessed by comparing basic demographic and clinical characteristics of responders and non-responders, as well as drop-outs and continuing participants, using *t*-tests (or Mann–Whitney U) and chi-squared tests as appropriate.

Primary and secondary outcome analyses will be carried out by fitting a linear mixed model to each outcome separately using all available data. A cell means model will be used to estimate mean scores for each group by time combination. An unstructured covariance type will be used to model the covariance structure among repeated measures and all models will be estimated by maximum likelihood. Group comparisons at post-baseline time points will be performed using contrasts within the proposed models. After inspection of the data, the appropriateness of stated methods will be revised, if necessary. Because of the number of significance tests for secondary outcomes, Hochberg’s modified Bonferroni procedure will be used so that the overall type I error rate does not exceed 0.05 [33].

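### Follow-up is dated from randomisation in usual care but from the first session in SurvivorCare, so the primary contrast carries an allocation-dependent time offset of up to two planned weeks, and non-attenders have no defined follow-up date

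*Protocol article*

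**What the plan says.** The arm-specific clock is stated consistently, so it is the design and not a slip.

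- Primary endpoint: Follow-up 1 falls "eight weeks after randomisation for the usual care group, and eight weeks after the first intervention session for the SurvivorCare group".
- Data collection procedure, text and Table 2: Follow-up 1 is "eight weeks after randomisation date for usual care patient or after the first session date for intervention patients", and Follow-up 2 is "six months after randomisation date for usual care patient or the first session date for intervention patients".
- Table 2, baseline, both arms: "on the day of randomisation (zero to two weeks before a potential first intervention session".
- Intervention group/SurvivorCare: "A nurse-led end of treatment session will take place in a standard timeframe after randomisation". No number of weeks is given there.
- Nurse-led telephone follow-up: the last of the three calls is seven weeks after the first session.
- Sample size requirements: the main contrast is the difference between arms at the first post-intervention follow-up.
- Statistical analysis: "Analyses will be by intention-to-treat". The method is a linear mixed model with one mean per group-by-time cell, fitted to all available data. No term for actual elapsed time is described.

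**The concern.** Randomisation makes the arms comparable at a given time after randomisation. Here the assessment time itself depends on the allocated arm. SurvivorCare can be measured at the same time as usual care or later, never earlier. If distress drifts after treatment ends, whatever drift occurs in the extra days is credited to, or charged against, the intervention. A model with nominal visits cannot separate the two.

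The second issue is that the SurvivorCare anchor is an event after randomisation that may not happen. A SurvivorCare patient who attends no session has no Follow-up 1 or Follow-up 2 date under the rule as written, whereas every usual care patient has both. If such patients went unmeasured, the loss would fall in one arm only and would depend on attendance.

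**Working it through.** **Plan's own figure.** Inputs from Sample size requirements: difference 3.6, SD 8.6, 80% power, two-sided alpha 0.05.

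- n per arm = 2 × (1.96 + 0.8416)² × 8.6² / 3.6² = 89.6, so 90 per arm and 180 in total. With 10% attrition, 180 / 0.9 = 200. The stated 180 and 200 reproduce.
- Standard error of the contrast: SE = 8.6 × √(2/90) = 1.28.

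**Planned timing, in weeks from randomisation** (Table 2; telephone follow-up section).

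| | Usual care | SurvivorCare |
|---|---|---|
| Baseline | 0 | 0 |
| First session | none | 0 to 2 |
| Last call (session + 7) | none | 7 to 9 |
| Follow-up 1 | 8 | 8 to 10 |

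The offset is 0 to 2 weeks, at most 2/8 = 25% of the usual care interval. At Follow-up 2 the same two weeks is about 2/26 = 8% of six months.

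**Bias.** Expected difference at Follow-up 1 = treatment effect + (drift per week × gap in weeks). The documents give no drift, so the values below are assumptions. The gap is set at the full two weeks for every SurvivorCare patient. With b the absolute bias and Φ the standard normal distribution function:

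- Type I error = 1 − Φ(1.96 − b/SE) + Φ(−1.96 − b/SE)
- Power = Φ((3.6 ± b)/SE − 1.96)

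| Drift, points/week (assumed) | Bias, points | Share of 3.6 | Type I error | Power if drift opposes effect | Power if drift adds to effect |
|---|---|---|---|---|---|
| 0.05 | 0.1 | 3% | 0.051 | 0.78 | 0.82 |
| 0.1 | 0.2 | 6% | 0.053 | 0.76 | 0.84 |
| 0.2 | 0.4 | 11% | 0.061 | 0.70 | 0.88 |
| 0.3 | 0.6 | 17% | 0.075 | 0.65 | 0.91 |

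Without drift, power at 90 per arm is 0.80. With a one-week gap the bias halves to 0.05 to 0.3 points, and type I error is 0.050 to 0.056. If the wait reached four weeks (an assumption beyond Table 2), drift of 0.2 points per week would give 0.8 points (22% of 3.6) and type I error 0.096.

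**Non-attenders.** The documents give no attendance rate. If 5%, 10% or 20% of the SurvivorCare arm had no Follow-up 1, that arm would fall from 90 to 85.5, 81 or 72, and power to 0.79, 0.78 or 0.75. The loss of power is small. The selective loss in one arm is the larger worry, and it cannot be sized from the documents.

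**Common clock.** With the same interval from randomisation in both arms, the gap is 0, the time-related bias is 0, and the sample size is unchanged.

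**The case against.** The strongest defence is that the rule has a purpose. The last call comes seven weeks after the session, so session plus eight weeks measures every attender after the whole intervention. A plain eight weeks from randomisation would catch a patient with a two-week wait at session plus six, before that call. This stands, but it constrains the choice of common anchor and does not justify two clocks.

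Table 2 also limits the planned gap to two weeks, and no section reports or expects delays. A reader might infer a far longer wait from Recruitment process ("Patients are approached zero to six months prior to the end of treatment (preferably), or up to six months after the end of treatment"), but that window concerns approach and not randomisation. The limit stands as a plan. The rule itself does not cap the interval if a session slips.

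A reader might also infer that the bias is large. Drift of 0.5 points per week over two weeks gives 1.0 point, or 28% of 3.6. It also means usual care falls 0.5 × 8 = 4.0 points in eight weeks, more than the effect the trial seeks. Nothing in the documents supports such a rate.

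Nor do they support a claim that the bias must favour SurvivorCare. Patients may enter before or after treatment ends, and the telephone follow-up section itself mentions feelings of abandonment after completion. Distress could rise in some.

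Finally, re-dating an open trial at 18 sites with several ethics approvals has a cost, and patients already followed cannot be re-dated. This stands and shapes the fix.

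**Conclusion.** The asymmetry is certain: 8 weeks against a planned 8 to 10 for the primary contrast, in one direction only, with nothing in the described model to remove it. Its size and sign are not known. Under assumed drift of 0.05 to 0.3 points per week and the full two-week gap, the bias is 0.1 to 0.6 points against a standard error of 1.28, with type I error 0.051 to 0.075. If sessions run promptly and drift is slow, the bias is modest.

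On non-attenders, a reader might infer that they are dropped and that intention-to-treat is therefore broken. The article does not say so. It promises intention-to-treat, all available data and an assessment of drop-out bias, and the full protocol may hold a fallback date. What it does show is a rule that leaves their follow-up date undefined, so the intention-to-treat analysis is at risk, not breached.

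Severity: should-fix.

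**What to change.** For patients not yet randomised, date Follow-up 1 and Follow-up 2 in both arms from one anchor that does not depend on allocation. There are two options:

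- a provisional session date booked for every patient before randomisation, in line with the potential session date that Table 2 already mentions; or
- a single common interval from randomisation, long enough to fall after the last call. With the planned wait of up to two weeks, that call comes as late as 2 + 7 = 9 weeks, so the interval must exceed 9 weeks.

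Send questionnaires on these same dates to SurvivorCare patients who have no session.

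For all patients, including those already followed under the current rule, record completion dates, report elapsed time since randomisation by arm, and run a sensitivity analysis of the primary contrast using actual weeks since randomisation.

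Cost: a short amendment across sites and a changed mailing schedule, with no extra patients or visits. The trial will contain two schedules, which the elapsed-time report and sensitivity analysis should make visible, and some SurvivorCare patients will not be assessed exactly eight weeks after their session.

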#### Secondary endpoints

Compared to patients in control groups, patients allocated to SurvivorCare will report:

(i) Significant beneficial effect for unmet psychological and informational needs, and quality of life from Baseline to Follow-up 1;

(ii) Sustained improvement in psychosocial outcomes over six months.

## Methods

### Design and setting

The study is being undertaken at 18 sites within Australia. Peter MacCallum Cancer Centre is the coordinating site, with all participant data stored centrally. A feasibility survey was conducted in January 2009. Sites were selected based on their proximity to patients in addition to the availability of at least one nurse to administer the SurvivorCare intervention. Ideally, the nurse would be a specialist colorectal cancer nurse; however, nurses with general oncology experience were also eligible. Availability of site resources/space to conduct the study was also considered.

Ethical approval was obtained individually by the Human Research Ethics Committees of Victorian and Tasmanian sites, and a central governance approval was obtained for all sites in New South Wales.

### Participants

To be eligible, participants need to: (1) have a confirmed diagnosis of colon or rectal cancer; (2) have stage I to III disease (that is, non-metastatic); (3) be treated with curative intent with surgery +/− radiation +/− chemotherapy; (4) be over 18 years; and (5) be able to understand English. Exclusion criteria are (1) demonstrated cognitive or psychological difficulties as defined by the treatment team’s assessment or documented within the patient’s medical history; (2) too unwell to participate in the study as determined by the patient’s treatment team; (3) past history of malignancy other than non-melanomatous skin cancer; (4) enrolment in a conflicting supportive care trial that might impact the study’s measured endpoints.

